## Abstract

**Background:**

Corona Virus Disease 19 (COVID-19) is a new pandemic, declared a public health emergency by the World Health Organization, which could have negative consequences for pregnant and postpartum women. The scarce evidence published to date suggests that perinatal mental health has deteriorated since the COVID-19 outbreak. However, the few studies published so far have some limitations, such as a cross-sectional design and the omission of important factors for the understanding of perinatal mental health, including governmental restriction measures and healthcare practices implemented at the maternity hospitals. Within the Riseup-PPD COST Action, a study is underway to assess the impact of COVID-19 in perinatal mental health. The primary objectives are to (1) evaluate changes in perinatal mental health outcomes; and (2) determine the risk and protective factors for perinatal mental health during the COVID-19 pandemic. Additionally, we will compare the results between the countries participating in the study.

**Methods:**

This is an international prospective cohort study, with a baseline and three follow-up assessments over a six-month period. It is being carried out in 11 European countries (Albania, Bulgaria, Cyprus, France, Greece, Israel, Malta, Portugal, Spain, Turkey, and the United Kingdom), Argentina, Brazil and Chile. The sample consists of adult pregnant and postpartum women (with infants up to 6 months of age). The assessment includes measures on COVID-19 epidemiology and public health measures (Oxford COVID-19 Government Response Tracker dataset), Coronavirus Perinatal Experiences (COPE questionnaires), psychological distress (BSI-18), depression (EPDS), anxiety (GAD-7) and post-traumatic stress symptoms (PTSD checklist for DSM-V).

**Discussion:**

This study will provide important information for understanding the impact of the COVID-19 pandemic on perinatal mental health and well-being, including the identification of potential risk and protective factors by implementing predictive models using machine learning techniques. The findings will help policymakers develop suitable guidelines and prevention strategies for perinatal mental health and contribute to designing tailored mental health interventions.

**Trial registration:**

ClinicalTrials.gov Identifier: NCT04595123.

## Background

Corona Virus Disease 19 (COVID-19) is a new pandemic, declared a public health emergency by the World Health Organization, which could have negative consequences for pregnant and postpartum women [1]. Although pregnant women do not seem to be more likely to contract the infection than the general population [2–4], obstetric complications have been detected in infected pregnant women, including the threat of premature delivery, caesarean delivery and maternal complications in the postpartum period [3, 5]. Antenatal or intrapartum vertical transmission (transmission from a woman to her newborn) might also be possible and can result in severe consequences for the newborn [6, 7].

In light of the unprecedented crisis brought about by the COVID-19 pandemic, many perinatal healthcare practices have been changed in an attempt to reduce the risk of transmission of the novel coronavirus. These include cancelation of prenatal and postpartum courses routinely provided to mothers, adjustments to prenatal and postpartum appointments, restrictions to the partner’s presence during childbirth and postpartum visitation and, in some cases, face-to-face consultations replaced by teleconsultations [8, 9]. At the same time, the confinement and social distancing measures implemented to contain the spread of COVID-19 have been particularly challenging for women during the perinatal period [10]. The lack of information about this new virus, the social isolation and perceived loneliness, women’s worries over their own health and fear of infection and transmission of the virus to their fetus/newborn, together with sudden changes in maternity-care practices, may result in increased psychological distress during the perinatal period [11].

The perinatal period (from pregnancy to 1 year after childbirth) is, in general, a vulnerable time for the acute onset and recurrence of mental disorders. According to pre-pandemic data, it is estimated that 1 in 5 women will develop a mental disorder in the perinatal period [12–15]. Perinatal depression is the most common disorder during pregnancy and the postpartum period and carries long-lasting adverse effects for women, their partners and their infants, while also imposing a strong burden on their families and society as a whole [16]. The scarce evidence published to date suggests that mental disorders in pregnant women have increased since the COVID-19 outbreak. Studies conducted in Canada [17], China [18], Turkey [19, 20] and Italy [21] report that the rates of depression and anxiety in pregnant women more than doubled compared to studies prior to the pandemic. However, the few studies published so far have some limitations, such as a cross-sectional design, small sample sizes, the absence of assessment throughout the postpartum period or the omission of important factors for the understanding of perinatal mental health, including governmental restriction measures, healthcare practices implemented at the maternity hospitals and women’s coping strategies. Thus, further research using prospective comprehensive assessments, examining women’s psychological distress, as well as potential risk and protective factors, is needed in order to provide an evidence-based foundation for the understanding of the impact of the COVID-19 pandemic on women’s perinatal mental health [11, 22].

In order to investigate and recommend best practices that may mitigate the impact of the COVID-19 pandemic on women’s mental health [11, 23], members of the “Research Innovation and Sustainable Pan-European Network in Peripartum Depression Disorder – Riseup-PPD” (Cost Action 18138), funded by the Horizon 2020 Framework Programme of the European Union, established the “Perinatal Mental Health and COVID-19 Pandemic” Task Force. Currently, the research team is conducting an international prospective cohort study aimed at filling the gaps in research on the impact of the COVID-19 pandemic on perinatal mental health (Riseup-PPD-COVID-19), and this article presents the study protocol.

## Methods

### Aim

The main aim of this prospective study is to investigate the impact of the COVID-19 pandemic on perinatal mental health (depression, anxiety, and post-traumatic stress symptoms).

The primary objectives are the following:
To evaluate changes in perinatal mental health outcomes (symptoms and indices of clinical risk for mental disorders) during the COVID-19 pandemic.

We will evaluate the changes in (a) perinatal mental health symptoms (depression, anxiety and post-traumatic stress disorder [PTSD]); and (b) clinical risk indices (proportion of women above the clinical cut-off point on a validated self-report scale) for depression and anxiety disorders. We will compare the results to similar pre-pandemic studies in all the countries. We will also assess the acute and long-term mental health impact of different phases of the COVID-19 pandemic by measuring the changes in perinatal mental health outcomes between the initial survey and the follow-up assessments.
2)To determine the risk and protective factors that predict perinatal mental health outcomes during the COVID-19 pandemic.

We will determine the risk and protective factors that predict PTSD symptoms and the clinical risk of depression and anxiety disorders (proportion of new cases above the cut-off point on validated self-report scales in the follow-up period) during the COVID-19 pandemic. Factors included in our study were based on recent literature [24–28] and include demographic variables, COVID-19 epidemiology and public health measures, perinatal experiences during the COVID-19 pandemic, and psychological distress.

Furthermore, additional secondary objectives related to the impact of COVID-19 on perinatal mental health will also be examined: the comparison of perinatal mental health outcomes between the countries participating in the study; breastfeeding and its protective role in perinatal mental disorders; the risk of perinatal mental disorders in COVID-19-positive women vs. COVID-19-non-positive women; and factors associated with the level of distress of women during the perinatal period.

We hypothesize an increase in negative perinatal mental health outcomes (symptoms and clinical risk) among women during the COVID-19 pandemic. We also hypothesize that common risk factors (e.g., low income, low social support, high level of psychological distress, previous history of mental disorders) will be associated with an increase in the clinical risk of depression and anxiety during the COVID-19 pandemic. Additionally, we hypothesize that pandemic-related risk factors, such as being exposed to and/or having a positive diagnosis for COVID-19, will be associated with increased risk of perinatal mental disorders.

### Study design

This is an international prospective observational cohort study, with a baseline and three follow-up assessments: at one, three, and six months post-baseline. The observation period will be 6 months, from the initial evaluation to the last follow-up assessment. The overall study will span from 15 June 2020 to 15 June 2021.

### Setting

This international study will be carried out in 11 European countries (Albania, Bulgaria, Cyprus, France, Greece, Israel, Malta, Portugal, Spain, Turkey and the United Kingdom), Argentina, Brazil and Chile.

### Participants

The study population consists of women during the perinatal period. The rationale is to evaluate women throughout their pregnancy and during 1 year after childbirth, for a six-month period (from baseline to follow-up). Women can, thus, enter the study during pregnancy or at any time during the first 6 months following childbirth [29].

The inclusion criteria at baseline are:
Being pregnant or a biological mother of a child six months of age or youngerWomen 18 years of age or olderLiving in one of the countries involved in the studyConsenting to participate in the study

The exclusion criteria are:
Not being currently pregnant or not being the biological mother of a child six months of age or youngerWomen younger than 18 years of ageLiving in a country that does not participate in the study.Not consenting to participate in the study

### Sample size

We have not set any restrictions on participant enrollment. However, a representative sample size was calculated according to the number of newborns in the previous year in each country. Thus, we estimated a minimum sample size of 300 participants per country, based on an α-level of 0.05 and heterogeneity equal to 50%.

### Variables and measures

The variables and measures planned for the different phases of the study are presented in Table 1.

**Table 1 Tab1:** Variables and measures used in each phase of the study

Variables	Measures	Baseline	T1	T2	T3
*Independent/predictor*					
COVID-19 epidemiology and public health measures	OxCGRT	X	X	X	X
Demographic variables	14 questions	X			
Perinatal health care experiences related with COVID-19	COPE-IS	X			
COVID-19 exposures and symptoms	COPE-IS; COPE-IU	X	X	X	X
COVID-19 financial impact	COPE-IS; COPE-CF	X	X	X	X
COVID-19 social support impact	COPE IS; COPE-CF	X	X	X	X
COVID-19 coping strategies	COPE-IS; COPE-IU	X	X	X	X
COVID-19 emotional impact	COPE-IS; COPE-IU	X	X	X	X
Health background, mental health, and substance use	COPE-IS	X			
Psychological distress	BSI-18	X	X	X	X
*Dependent/outcome*					
Depression symptoms	EPDS	X	X	X	X
Anxiety symptoms	GAD-7	X	X	X	X
PTSD symptoms	10 questions from PTSD Checklist for DSM-5 included in COPE-IS; COPE-IU	X	X	X	X

T1: 1-month follow-up; T2: 3-month follow-up; T3: 6-month follow-up; PTSD: Post-traumatic Stress Disorder; OxCGRT: Oxford COVID-19 Government Response Tracker; COPE-IS: Coronavirus Perinatal Experiences - Impact Survey; COPE-IU: Coronavirus Perinatal Experiences Scale - Impact Update; COPE-CF: Coronavirus Perinatal Experiences Scale - Care Follow Up; BSI-18: Brief Symptom Inventory-18; EPDS: Edinburgh Postnatal Depression Scale; GAD-7: Generalized Anxiety Disorder Screener

### Independent/predictor measures

#### Oxford COVID-19 government response tracker (OxCGRT)

We will collect the following macro variables related to the COVID-19 epidemiological data and public health measures publicly available for each of the participating countries from the Oxford COVID-19 Government Response Tracker (OxCGRT) [30]: (1) Population; (2) Number of confirmed deaths; (3) Number of confirmed COVID-19 cases; (4) Case fatality rate; (5) Government Stringency Index [30], a composite score from 0 to 100 that considers the strictness of containment strategies (closures, movement restrictions) and information campaigns; (6) Containment and Health Index [30], a composite measure which combines ‘lockdown’ restrictions and closures with measures such as testing policy and contact tracing, short term investment in healthcare, as well investments in vaccines; and (7) Stay-at-home requirements or household lockdowns, which include: (a) No measures; (b) Recommended not to leave the house; (c) Required to not leave the house with exceptions for daily exercise, grocery shopping, and ‘essential’ trips; (d) Required to not leave the house with minimal exceptions (e.g., allowed to leave only once every few days, or only one person can leave at a time, etc.). These data will be extracted according to the date of the baseline and subsequent follow-up analysis.

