##### COVID-19 exposures and symptoms

Six items about (1) the diagnosis of COVID-19; (2) any symptoms compatible with the coronavirus disease; (3) contact with someone who has been diagnosed with COVID-19; (4) any death of family or friends due to COVID-19; (5) the level of distress about COVID-19-related symptoms or potential illness: (5a) their own illness or (5b) in their friends and family [31, 32].

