### Data analysis

Patterns of missingness in the data will be studied and the Expectation-Maximization algorithm will be implemented to impute missing data. Attrition analyses will be carried out to examine differences between participants who completed all the assessments and those who did not. Descriptive statistics will be examined for the study variables for all the assessment times. Measurement equivalence will be studied in order to ensure we are measuring the same variables across countries.

Changes in mental health between baseline and the follow-ups will be examined by testing latent growth curve models for each outcome. Moreover, the relationships between the rates of change in predictors (i.e., risk and protective factors) and mental health results during the follow-up will be analyzed. Multilevel analyses will be performed to control the moderation of demographic variables in those interrelations. Regarding the overall fit of these models, Satorra-Bentler χ^2^, CFI, RMSEA and the confidence interval for the RMSEA statistics will be calculated. Lagrange multipliers and the Wald test will be performed sequentially to improve the fitness of the models, following the hypotheses of the study. Standardized coefficients and measurement equations with scores in R^2^ will be reported. These analyses will be undertaken using the statistical program EQS. 6.3.

To determine the risk and protective factors to predict perinatal mental health outcomes during the COVID-19 pandemic, a random sample of 70% of the data will be used to derive the machine learning algorithms including regularized logistic regression, random forest, decision tree, and gradient boosting to predict the risk of PPD, and their performance, and the remaining 30% for validation. First, in the derivation sample, all the predictors described above will be entered into the models to estimate the probability of depression or anxiety or PTSD. Beginning with a model containing all potential covariates, the variable with the least significant *P* value will be removed and tested using the likelihood-ratio test until all variables left in the model significantly (at alpha = 0.05) contribute to the model.

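### National case and death counts, listed as predictors with population as a separate item and no per-capita form, mix country size with epidemic intensity; define them as rates over a stated window

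*Protocol article*

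**What the plan says.** In the protocol article, the OxCGRT subsection stands under the heading for independent/predictor measures. It opens with "We will collect the following macro variables related to the COVID-19 epidemiological data and public health measures" and describes the data as "publicly available for each of the participating countries from the Oxford COVID-19 Government Response Tracker (OxCGRT"). The first four of seven items are "1) Population; (2) Number of confirmed deaths; (3) Number of confirmed COVID-19 cases; (4) Case fatality rate". The other three are two policy indices and the stay-at-home category. On timing it says "These data will be extracted according to the date of the baseline and subsequent follow-up analysis", without stating whether the counts are new or cumulative.

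Table 1 places COVID-19 epidemiology among the predictors at baseline and at all three follow-ups. The Data analysis section says that "all the predictors described above will be entered into the models to estimate the probability of depression or anxiety or PTSD". It then removes the variable with the weakest P value, step by step, until all those left are significant at 0.05. No rescaling of the macro variables is described.

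The Setting section names "11 European countries (Albania, Bulgaria, Cyprus, France, Greece, Israel, Malta, Portugal, Spain, Turkey and the United Kingdom), Argentina, Brazil and Chile", that is 11 + 3 = 14 countries.

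**The concern.** Objective 2 names COVID-19 epidemiology among the candidate risk and protective factors. The quantity of interest is how intense the epidemic was around the woman at the time of assessment. A national count is population multiplied by incidence, so between countries it carries both. A coefficient or importance value for such a count cannot be read as an effect of the epidemic. Part of a difference between large and small countries could be reported as one, and a real effect of incidence could be diluted.

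The article does define a ratio where it wants one (case fatality rate), but none for cases or deaths per head. The Data analysis section also plans scores for clinical use and nomograms. A score containing a national count would not carry over to a country of another size.

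**Working it through.** The plan gives no figure to reproduce here, and it states no populations or incidences. All magnitudes below rest on assumptions, labelled as such.

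**1. What a count measures.** Let P be population, r incidence and m mortality per head. Cases C = P × r and deaths D = P × m. Case fatality rate is D/C = m/r, so population cancels and that item does not scale with size.

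**2. Equal exposure, different counts.** Assume populations of 0.5 million and 200 million and an incidence of 1,000 per 100,000 in both.
- 500,000 × 0.01 = 5,000 cases
- 200,000,000 × 0.01 = 2,000,000 cases
- Ratio 2,000,000 / 5,000 = 400 at identical incidence

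**3. Does a separate population term repair this?** With untransformed terms the linear predictor is b1·C + b2·P = P·(b1·r + b2).
- Two countries with the same r differ by (P1 − P2)·(b1·r + b2). This is zero only at the single incidence r = −b2/b1.
- One unit of r shifts the predictor by b1·P, which is 400 times as much in the larger country of step 2.
- If population is eliminated and cases stay, b2 = 0 and the difference at equal r is b1·r·(P1 − P2), with no size adjustment.

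With logged terms, g1·log C + g2·log P = g1·log r + (g1 + g2)·log P. Here g1 is exactly the coefficient of log incidence, provided that log P stays in the model.

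**4. How far counts follow size or incidence.** Assume that log population (SD sp) and log incidence (SD sr) are independent across countries. Then
- corr(log C, log P) = sp / √(sp² + sr²)
- corr(log C, log r) = sr / √(sp² + sr²)

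For example, with sp = 1.5 and sr = 0.5 these are 1.5/1.581 = 0.95 and 0.5/1.581 = 0.32. The last column is from a simulation of 14 countries (3,000 runs per setting). It gives the mean R² when incidence is regressed on untransformed cases and population.

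| sp | sr | count with size | count with incidence | R² (adjusted) |
|---|---|---|---|---|
| 1.0 | 0.3 | 0.96 | 0.29 | 0.66 (0.60) |
| 1.0 | 1.0 | 0.71 | 0.71 | 0.71 (0.66) |
| 1.0 | 1.5 | 0.55 | 0.83 | 0.75 (0.70) |
| 1.5 | 0.5 | 0.95 | 0.32 | 0.52 (0.43) |
| 1.5 | 1.0 | 0.83 | 0.55 | 0.56 (0.48) |
| 2.0 | 0.3 | 0.99 | 0.15 | 0.41 (0.31) |
| 2.0 | 1.5 | 0.80 | 0.60 | 0.51 (0.42) |

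Over all settings tried (sp 1.0 to 2.0, sr 0.3 to 1.5), the correlation with size was 0.55 to 0.99 and with incidence 0.15 to 0.83. Mean R² was 0.41 to 0.75 (adjusted 0.31 to 0.70).

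**5. With rates.** C/P = r by construction. If incidence is independent of size, the correlation with log population falls to 0.

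**The case against.** The strongest reply is that the article says only that these variables are collected. Population beside cases and deaths is what one would extract in order to form rates, and the sentence entering all predictors cannot mean unprocessed values throughout: date of birth and city of residence are on the list too, and COPE scoring is still to be determined. A fuller plan, not shown, may define rates. This stands as far as it goes: that untransformed counts will be entered is an inference. It does not remove the point, because the article fixes a predictor list and a rule for using it, and rates are on neither.

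The reply also says that logged terms recover incidence exactly and that trees can approximate a ratio. Both are right, but the article states no log scale, and population remains open to elimination.

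A reader might infer that these predictors track country size instead of the epidemic. The documents do not support that. Size dominates only if population varies clearly more than incidence; at sp = 1.0 and sr = 1.5 the count follows incidence more closely (0.83 against 0.55). Within one country, change in a count reflects the epidemic, although across countries the size of that change still scales with population.

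A reader might also infer that the woman's own exposure goes unmeasured. It does not: the COPE items ask about diagnosis, symptoms, "3) contact with someone who has been diagnosed with COVID-19; (4) any death of family or friends due to COVID-19", and Table 1 schedules them at all four assessments. Finally, a reader might infer that the counts are running totals that can only rise. The article does not say so.

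**Conclusion.** The point holds for two of the seven macro variables, confirmed cases and confirmed deaths, and for population as a predictor in its own right. Used as listed, they mix country size with epidemic intensity in between-country comparisons. An additive population term is only a partial remedy unless the terms are logged and population is kept.

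The 400-fold gap shows how counts scale at equal incidence; it is not an estimate of bias in any coefficient or AUC. The share of incidence variance recovered (41 to 75%, adjusted 31 to 70%) depends on the assumed spreads, on independence of incidence and population, and on untransformed linear terms. The direction of the problem does not depend on those figures. Case fatality rate, both policy indices, the stay-at-home category and the woman-level exposure items are unaffected.

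**What to change.** In the OxCGRT subsection, define the epidemic predictors as new confirmed cases and new confirmed deaths per 100,000 population over a stated window before each woman's questionnaire date. Fourteen days is one example; what matters is that the window is fixed in advance. Cumulative rates per 100,000 to the same date can be added if long-term burden is of interest. Use population only as the denominator and take it off the list of candidate predictors.

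The cost is two derived variables from data already being extracted, and one sentence of text. Short windows carry some reporting noise. The measure also remains national, so it will not describe the epidemic in a woman's own region. If rates were intended all along, the same sentence settles the matter.
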